## Abstract

**Introduction:**

Care transitions, particularly hospital discharge, present significant risks to patient safety. Deficient medication-related discharge communication is a major contributor, posing substantial risk of harm to older patients. This protocol outlines the Improved Medication communication and Patient involvement At Care Transitions (IMPACT-care) intervention study, designed to evaluate the effects of a multifaceted intervention for older hospitalised patients on medication-related discharge communication compared with usual hospital care.

**Methods and analysis:**

A pre–post intervention study will be conducted in two surgical and one geriatric ward of a university hospital in Sweden. The study will begin with a control period delivering usual care, followed by a training period and then an intervention period. The intervention comprises four components performed by clinical pharmacists: (1) information package provided to patients and/or informal caregivers, (2) preparation of medication-related discharge documentation, (3) facilitation of discharge communication and (4) follow-up call to patients or their informal caregiver. Eligible participants are aged ≥65 years, manage their own medications independently or with informal caregiver support, and are admitted to the study wards. Each study period (control and intervention) will last until 115 patients have been included. The primary outcome is the quality of medication-related discharge documentation, assessed using the Complete Medication Documentation at Discharge Measure (CMDD-M). Secondary outcomes include patients’ perceptions of knowledge and involvement in discharge medication communication, and their sense of security in managing medication post-discharge; adherence to medication changes from hospitalisation that persist after discharge; and unplanned healthcare visits following discharge. A process evaluation is planned to explore how the intervention was implemented. Patient inclusion began in September 2024.

**Ethics and dissemination:**

The study protocol has been approved by the Swedish Ethical Review Authority (registration no.: 2023-03518-01 and 2024-04079-02). Results will be published in open-access international peer-reviewed journals, and presented at national and international conferences.

**Trial registration number:**

NCT06610214.

STRENGTHS AND LIMITATIONS OF THIS STUDYUses a comprehensive, multifaceted intervention designed to address gaps in medication communication both during hospitalisation and after discharge.Conducted in both non-surgical and surgical wards, increasing the generalisability of findings to other healthcare settings.The inclusion of a process evaluation provides insights into the implementation and adherence to intervention components, offering valuable information to understand and interpret the study findings.The pre–post design without randomisation limits the ability to establish causal relationships between intervention and observed outcomes.Due to the complex, multifaceted nature of the intervention, it is not possible to determine which specific intervention components contribute most to the observed effects.

## Introduction

 The ageing population is rapidly increasing, with individuals aged 65 and older expected to rise from 10% in 2022 to 16% by 2050.^1^ Older adults frequently experience multiple chronic conditions, making them two times as likely to require hospital care compared with younger adults.^2^ Medications are a primary treatment for many health conditions, and as the prevalence of multiple illnesses increases, so does the use of medications, increasing the risk of medication-related complications.^3 4^ One in six hospital admissions and one in five readmissions among older patients are medication-related,^5 6^ most of which are preventable.^7^ Care transitions, particularly hospital discharges, pose significant risks to patient safety and are highlighted by the World Health Organization as a focus for healthcare improvements.^8^ More than one-third of older patients experience adverse drug reactions within 8 weeks post-discharge,^9^ often attributed to poor communication and coordination between hospitals, subsequent healthcare providers and patients or their informal caregivers.^610^,^13^ Most hospitalised older patients experience changes to their medication regimens, which persist after discharge and should be effectively communicated to all individuals involved in their care.^14 15^

Relying on written discharge notes and referrals to bridge communication gaps regarding medication changes and follow-up plans has proven unreliable, as this information is often delivered late or of insufficient quality.^16^,^19^ Discharge consultations often lack structure and patient-centredness, frequently being treated as a checklist item for healthcare professionals (HCPs) to complete before discharge.^20^,^22^ Physicians tend to adopt an authoritative role in medication discussions, which can discourage older patients from actively participating in their medication management.^23^ To foster patient involvement, HCPs should act as advocates rather than paternalistic figures.^24^ Patient-centred communication at discharge is essential for equipping patients with the knowledge and confidence to manage their medications and self-care.^20^ Involving patients in medical decisions is a key component of patient-centred care, leading to improved patient satisfaction and clinical outcomes, such as better glycaemic and blood pressure control.^25 26^ However, older patients may be less inclined or unable to participate actively, often due to factors such as cognitive or physical impairments.^27^ Many feel insufficiently empowered to engage in discussions about their medications and tend to rely on HCPs, following prescriptions without question.^22 28^ Even when discharge information is presented in a structured format, older patients frequently struggle to retain details about their medications.^29^ Informal caregivers can be vital in supporting patient involvement and bridging communication gaps between HCPs and older patients.^12 23^

To address these issues, the research project Improved Medication communication and Patient involvement At Care Transitions (IMPACT-care) was initiated.^30^ The project began with exploratory studies of the discharge communication,^12 19 22^ ultimately leading to the development of the intervention presented in this protocol.

### Aims and objectives

The overall aim is to evaluate the effects of a multifaceted intervention on improving medication-related discharge communication for older hospitalised patients, compared with usual hospital care.

The primary objective is to assess the intervention’s impact on the quality of written medication-related discharge documentation compared with usual hospital care. Secondary objectives include evaluating the intervention’s effect on patients’ perceived involvement in discharge medication communication and their confidence in post-discharge medication management, as well as adherence to medication changes from hospitalisation that persist after discharge and the need for unplanned healthcare visits following discharge, all in comparison to usual hospital care.

## Methods and analysis

This protocol was developed and reported in accordance with the Standard Protocol Items: Recommendations for Interventional Trials (SPIRIT) 2013 statement,^31^ the SPIRIT-outcomes 2022 extension,^32^ and the Template for Intervention Description and Replication checklist.^33^

### Study design

This prospective intervention study uses a pre–post design (figure 1). Control patients will be enrolled first (control period), followed by a training phase during which HCPs in the study wards will be trained to implement the intervention. Once the HCPs have undergone training sessions, the intervention period will start. Enrolment during both the control and intervention period will stop once the target sample size is reached, with patient follow-up continuing for 4 months post-discharge. Based on the pilot study, the control and intervention periods are each expected to last approximately 6 months, and the training phase will last around 2 months. Figure 1 provides a schematic overview of the study design. Study enrolment began in September 2024, and recruitment of participants for the intervention group is currently ongoing as of April 2025.

**Figure 1 F1:**
[figure not shown]
Schematic overview of the study design. ^α^CMDD-M, a point-based instrument using data from the patient’s electronic health records. ^β^PIMCH-Q, a questionnaire to patients measuring their perceptions of involvement in discharge medication communication and their confidence in post-discharge medication management. ^γ^Data on lasting medication changes from the patient’s electronic health records are compared with pharmacy dispensing data collected 120 days post-discharge. ^δ^Unplanned hospital revisits and medication-related readmissions up to 90 days post-discharge. CMDD-M, Complete Medication Documentation at Discharge Measure; HCPs, healthcare professionals; IMPACT-care, Improved Medication communication and Patient involvement At Care Transitions; PIMCH-Q, Patient Involvement in Medication Communication at Hospital discharge Questionnaire.

#### Rationale for study design

A randomised trial was deemed infeasible—neither at the patient level, due to contamination risks, nor at the ward level or as a stepped-wedge design, as these would require a large number of wards and exceed available resources. Consequently, a pre–post study design was selected, complemented by an interrupted time series (ITS) analysis for exploratory purposes. The ITS analysis, analysing data at regular intervals both before and after the intervention, allows for a more nuanced interpretation of the primary results by accounting for potential seasonal variations and changes in effect over time.

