### Sample size calculation

The sample size calculation is based on the primary outcome, which is the quality of medication-related discharge documentation measured using the CMDD-M. The intervention will be deemed successful if the average score is significantly higher in the intervention group compared with the control group. For the calculation, we assumed an evenly distributed sample between the two groups and set the target difference in CMDD-M scores at 1 point. This conservative target was chosen as it represents the smallest measurable step in the instrument. In practice, a 1-point difference may indicate the inclusion of medication changes in the discharge letter or discharge summary. Such an improvement reflects a critical enhancement in quality, with important implications for patient safety and continuity of care. Data from the pilot studies indicated that the baseline value for CMDD-M was 3.9 (SD 2.6) ([name], [name], [name], [name], *et al*: Facilitating patient empowerment at hospital discharge: A pilot study testing the feasibility of the IMPACT-care intervention, unpublished). Due to the maximum score limit in CMDD-M, the variance in scores is expected to differ between the control and intervention periods. This difference arises as scores may cluster near the upper limit, particularly in the intervention period where improved performance is anticipated, potentially leading to reduced variability compared with the control period. A two-sided t-test with Welch’s correction for df (to account for the variance difference between groups) was used. A power of 0.8 was considered sufficient to detect an increase, with a 5% two-sided significance level. Based on these assumptions, a sample size of 115 patients per group, for a total of 230 patients, is required.

Additionally, a permutation test using the Mann-Whitney U test was performed to assess the robustness of the t-test, yielding similar results.

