#### Exploratory analyses

To analyse data collected at multiple regular intervals before and after the intervention, an ITS analysis will be performed. A linear regression model will be estimated as follows:

$$\begin{array}{l} Y=b_{0}+b_{1}T+b_{2}I+e \end{array}$$

where:

Y: outcome variable (CMDD-M score, prevalence of patients achieving the maximum score on CMDD-M, PIMCH-Q score or the number of non-adherence instances to medication changes persisting post-discharge)

b_0_: intercept, representing the expected value of the outcome variable (Y) at baseline (T=0 and I=0).

b_1_: time effect, indicating the change of the outcome variable (Y) for each day passed, regardless of the intervention.

T: time in days passed from the start of the study, capturing natural changes in the outcome over time.

b_2_: intervention effect, representing the difference in the outcome variable (Y) between pre-intervention (I=0) and post-intervention (I=1) periods, after accounting for time trends.

I: dummy variable indicating whether the observation was collected before (0) or after (1) intervention, enabling comparison outcomes before and after the intervention.

e: error term, capturing random noise or unexplained variation in the outcome variable (Y).

This model will allow us to investigate whether there is an immediate effect following the intervention. Results will be presented as regression estimates with 95% CI and p values. This analysis will be conducted for the following outcomes: CMDD-M score, prevalence of patients achieving the maximum score on CMDD-M, PIMCH-Q score (the three dimensions separately and total score), the number of non-adherence instances to medication changes persisting post-discharge and prevalence of patients who are fully adherent to medication changes.

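### The exploratory interrupted time series model has one common slope, one step and no season term, so it cannot account for season or for a changing effect as the protocol says it does

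*Protocol article*

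**What the plan says.** Rationale for study design explains that randomisation was not feasible, so a pre-post design was chosen, "complemented by an interrupted time series (ITS) analysis for exploratory purposes". It says the ITS gives a more nuanced reading of the primary results by "accounting for potential seasonal variations and changes in effect over time".

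Exploratory analyses gives the model in full: Y = b0 + b1T + b2I + e, with T in days from study start and I the 0/1 period indicator. The coefficient b1 is the "time effect, indicating the change of the outcome variable (Y) for each day passed, regardless of the intervention". The same section describes what the model delivers more narrowly: "This model will allow us to investigate whether there is an immediate effect following the intervention".

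On timing, Study design says "the control and intervention periods are each expected to last approximately 6 months, and the training phase will last around 2 months", and "Study enrolment began in September 2024". Sample size calculation states that "a sample size of 115 patients per group, for a total of 230 patients, is required" and reports a pilot SD of 2.6 for the CMDD-M score. Primary outcome analysis is a separate linear regression with robust standard errors and does not use the ITS model.

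**The concern.** The two sections conflict. Without a time-by-intervention term, no change in effect can be estimated. Without a season term, only straight-line drift is absorbed. This is not detail left to the analysis plan, because the protocol publishes both the equation and the claim.

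The common slope also does harm of its own. Growth or decay of the effect within the intervention period is attributed to b1 and then projected back across the gap, which distorts b2. Some change in effect is plausible: pharmacists' experience varies, new staff are trained while the intervention runs, and regular meetings are held to remove barriers to implementation.

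The planned covariates contain no calendar time, so readers will turn to the ITS to judge whether the pre-post difference is a time artefact. If they believe it has dealt with season and changing effect, they may be wrongly reassured or wrongly alarmed.

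**Working it through.** The plan gives no figure for the ITS, so there is none to reproduce.

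**Inputs.** From the protocol: 115 patients per period, periods of about 6 months, a gap of about 2 months, SD 2.6. Assumed: even recruitment, SD 2.6 in both periods (the plan expects a smaller one under intervention), and the effect shapes and seasonal cycles below. Control occupies months 0-6 and intervention months 8-14. Mean times are 3 and 11, so they differ by 8. The variance of T within each period is 6²/12 = 3.

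**1. Changing effect.** In this balanced layout b1 is the mean of the two within-period slopes, and b2 = (difference in means) - 8 × b1.
- Growth from 0 to 2: mean effect 1.0; slopes 0 and +1/3 per month; b1 = 1/6. Then b2 = 1.0 - 8/6 = **-0.33**; the true step is 0.
- Fading from 2 to 0: mean effect 1.0; b1 = -1/6. Then b2 = 1.0 + 8/6 = **+2.33**; the true step is 2.
- Growth with other gaps: 1 month gives 1 - 7/6 = -0.17; 3 months gives 1 - 9/6 = -0.50.
- Constant effect of 1 and no season: b2 = 1.00, unbiased.

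With (T - T_start) × I added, both patterns are recovered exactly: step 0 with slope change +0.333 per month, and step 2 with slope change -0.333 per month.

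**2. Season.** Counting from 1 September, control covers September to February and intervention about May to October, so only September and October recur. Take no effect and an annual cycle of amplitude A. The worst phase crosses its mean at the midpoint of the gap.
- Pre-post difference: 2 × (2/π) × sin(120°) × A = 1.10A.
- Within-period slope, the same in both periods: -0.203A per month.
- b2 = 1.10A + 8 × 0.203A = **2.72A**.

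A day-based calendar gives 2.66A against 1.14A. In simulation at this phase, a false significant benefit appears in 11%, 34% and 87% of trials for A = 0.25, 0.5 and 1, against a nominal 2.5%. Other phases do less: a mid-April peak gives +0.81A. The slope-change term does not cure this (b2 about 2.8A). One annual harmonic added to the stated model raises the SE of b2 to 1.91.

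**3. Precision.**
- Pre-post: 2.6 × √(2/115) = 0.343.
- R² between T and I = 16/(16 + 3) = 0.842; variance inflation 19/3 = 6.33; √6.33 = 2.52.
- Stated model: SE(b2) = 0.343 × 2.52 = **0.863**; power for the 1-point target about 21%.
- With the slope change: the step compares the intervention line 3 months from its centre with the control line extrapolated 5 months from its centre. SE(b2) = 2.6 × √{[(1 + 9/3) + (1 + 25/3)]/115} = **0.885**, or 2.6% more.
- Mid-intervention effect from that model: control is extrapolated 8 months. SE = 2.6 × √{[1 + (1 + 64/3)]/115} = **1.17**; worst-phase seasonal bias about 3.9A (1.96 points at A = 0.5, against 1.36 for the stated b2).

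**The case against.** The strongest reply is that little depends on this analysis. It is labelled exploratory, the success criterion and primary model do not use it, and the article openly lists limited causal inference as a weakness. That stands, and it limits the seriousness of the point.

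A reader might infer more than the document supports:
- *The ITS claim is what justifies a non-randomised design.* It is not. The stated reasons are contamination, the number of wards needed and resources.
- *The model reverses the intervention effect.* In the growing-effect case the true immediate step is 0, so -0.33 has the opposite sign only to the average effect of 1.0. It is significantly negative in only 5.5% of simulated trials.
- *A linear model for proportions and counts is an error.* This is not shown. Data at regular intervals could mean aggregated proportions, and the main analyses of these outcomes already use logistic and quasi-Poisson models.
- *About 21% power is a planning fault.* No power is claimed for this analysis.

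The calendar is also approximate. Intervention recruitment was under way in April 2025, so the gap may have been nearer 1 month. At that gap the growth bias shrinks to -0.17 and worst-phase seasonal bias is 1.9A against 1.3A. Both remain.

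Finally, changes in effect might loosely mean drift in the outcome, which b1 does absorb if it is linear. The text says effect, however, and season would still be unaddressed.

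**Conclusion.** The rationale claims two properties that the published model lacks. Neither the season claim nor the changing-effect claim can stand beside Y = b0 + b1T + b2I + e.

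The consequence is conditional. With a constant effect and no seasonal pattern, b2 is unbiased though imprecise. With an effect moving by 2 points over the intervention period, b2 misses the true immediate step by about a third of a point (0.17 to 0.50 for gaps of 1 to 3 months). With an annual cycle at an unfavourable phase, the linear time term more than doubles the bias of the raw difference. These sizes rest on even recruitment, the stated period lengths and assumed effect shapes and amplitudes; the document has no seasonal data. The conflict between the two sections rests on none of them.

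This should be corrected, but it is not critical: the primary analysis is untouched, and what is at risk is how its result is interpreted.

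**What to change.** - **Model (Exploratory analyses).** Use Y = b0 + b1T + b2I + b3(T - T_start)I + e, with T_start the first day of the intervention period. Report b2 as the immediate step and b3 as the change in slope.
- **Claim (Rationale for study design).** Delete the statement that the ITS accounts for seasonal variation, and say that season cannot be separated from period in this design.
- **Interpretation.** State that b2 has about 2.5 times the standard error of the pre-post contrast, so a null ITS result does not refute the primary result.
- **Reporting.** Do not make the model-based mid-intervention effect a headline summary. If it is shown, give its standard error of about 1.17 and note its greater sensitivity to season.

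The cost is one model term, some rewording and about 3% more standard error on b2; no new data are needed. The slope change will itself be imprecise: its standard error over 6 months is about 1.19 points. Deleting the claims alone would remove the contradiction but leave b2 biased whenever the effect changes over time.

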### Settings

The study is conducted in two surgical wards and one geriatric ward at Uppsala University Hospital in Sweden. The surgical wards mainly handle emergency surgeries, as well as liver-pancreas, transplantation, oesophagus-stomach, endocrine and colorectal surgeries. The geriatric ward treats older patients with complex acute medical and rehabilitation needs. These two clinical specialties were selected to assess whether the intervention could have an effect across various clinical settings.

### Study population and recruitment

Patients aged 65 years or older, who manage their own medications either independently or with support from an informal caregiver and are admitted to the study wards, are eligible for inclusion. An informal caregiver is defined as an unpaid individual, often a family member, who assists the patient with daily activities, healthcare communication and medication management. Exclusion criteria apply if patients meet any of the predetermined conditions that would hinder the successful delivery of the intervention or the reliable collection of outcome data (a detailed list is provided in box 1).

Box 1The inclusion and exclusion criteria in the study. Patients meeting exclusion criteria 1–9 are excluded at the time of hospital admission, while those meeting exclusion criteria 10–15 are excluded at the time of dischargeInclusion criteria65 years or older. Manages their own medications, either independently or with support from an informal caregiver, prior to inclusion.Exclusion criteriaChecked at hospital admissionRegistered in a region outside the study hospital (limited data availability).Admitted from a nursing home (no own medication management prior to admission).Unable to receive information or provide consent independently (due to cognitive impairment or unresponsiveness).Already included in the study.Patient delocalised to the study ward with another medical discipline responsible for the patient’s care (formally, no study ward patient).In a late palliative phase prior to inclusion (intervention not suitable).Unable to communicate in Swedish (hindering intervention delivery).Has restricted personal information in the EHR (limited data availability).Admitted for transplantation (intervention not suitable).Checked at hospital dischargeDischarged to a nursing home (intervention not suitable).Patient transitions to late palliative phase during the hospitalisation (intervention not suitable).The patient is transferred to a non-study ward and is discharged from there (hindering intervention delivery).The patient dies during the course of the hospital stay (hindering intervention delivery).No medication changes that last post-discharge during the hospitalisation (intervention not suitable).The duration of stay on the study ward is less than 48 working hours (excluding time from 16:00 before weekends/public holiday to 08:00 the day after a weekend/public holiday) (hindering intervention delivery).EHR, electronic health records.

The researchers, who are employed by the hospital, screen the admission lists of the study wards daily on weekdays to identify eligible patients, who are then asked for inclusion by the researchers or clinical pharmacists on the ward. Eligibility is primarily determined through the patient’s electronic health records (EHR), with any uncertainties resolved through discussions with HCPs at the study wards. Once identified, patients are informed both verbally and in writing, and written informed consent (online supplemental material I) is requested. Patients meeting exclusion criteria 10–15 in box 1 are excluded at discharge.

During the recruitment of control patients, all patients fulfilling the inclusion and exclusion criteria are invited to participate. During the intervention period, patient inclusion is determined based on the capacity of the pharmacists performing the intervention. The pharmacists’ capacity will be evaluated through regular feedback discussions, ensuring that the inclusion process aligns with their workload. If the number of eligible patients exceeds the pharmacists’ capacity, the pharmacist, in collaboration with the research team, will determine how many eligible patients can be included. To prioritise which patients to include, a random priority number will be generated for each eligible patient at the study ward level using Microsoft Excel, with those assigned the highest priority included first.

